**Table 13 Definitions of Events**

| **Term** | **Definition** |
| --- | --- |
| **Adverse Event (AE)** | Standard: Any untoward medical occurrence in a participant to whom a medicinal product has been administered, including occurrences which are not necessarily caused by or related to that product.  Adapted: Any deterioration in mental state or behaviour in a participant to whom the intervention has been administered, including occurrences which are not necessarily caused by or related to the intervention. |
| **Adverse Reaction (AR)** | Standard: An untoward and unintended response in a participant to an investigational medicinal product which is related to any dose administered to that participant.  The phrase "response to an investigational medicinal product" means that a causal relationship between a trial medication and an AE is at least a reasonable possibility, i.e., the relationship cannot be ruled out.  All cases judged by either the reporting medically qualified professional or the Sponsor as having a reasonable suspected causal relationship to the trial medication qualify as adverse reactions.  Adapted: An untoward and unintended response in a participant to an intervention which is related to any feature of the digital intervention administered to that participant.  The phrase "response to an intervention" means that a causal relationship between an intervention and an AE is at least a reasonable possibility, i.e. the relationship cannot be ruled out.  All cases judged by the Sponsor as having a reasonable suspected causal relationship to the intervention qualify as adverse reactions. |

### 12.4 Recording and reporting of AEs and ARs

All AEs will be recorded within the app and reported to the Chief Investigator within 1 working day (24 working hours). If there is uncertainty that an AE event may reflect an AR, it will be reported to the Trial Steering Committee (TSC) and DMEC and if considered related to either of the apps, will be classified as an AR and reported to the trial Sponsor. who will escalate to the regulatory authority when considered appropriate.

In line with other complex intervention studies, we will monitor non-serious AEs and ARs that are not trial, or treatment related, serious deterioration, and active withdrawals from treatments. All occasions where the score on the PHQ-9 Q9 increases from 0/1 to 2/3 will be separately recorded. The reporting period for all events and reactions will be from first usage of the app until 10 weeks follow-up.

### 12.5 Responsibilities

Researchers at UNIEXE will check for AEs and ARs when participants complete treatment or at follow-up, potentially in response to automated feedback from the website.

Chief Investigator (CI) is responsible via liaison with research team to ensure all AEs are:

1. Recorded within 24 working hours/1 working day of becoming aware of the event and providing further follow-up information as soon as available.
2. Chased with the research team if a record of receipt is not recorded within 2 working days of initial reporting.
3. Distributed to the TSC for consideration if it meets criteria for an AR.
4. Disseminated to the Sponsor and Ethics committee where it is considered the AE may represent an AR.

Sponsor (NB where relevant these can be delegated to CI) is responsible for:

1. Central data monitoring and verification of ARs according to the trial protocol.
2. Reporting safety information to the PI, delegate or independent clinical reviewer for the ongoing assessment of the risk/benefit according to the Trial Monitoring Plan.
3. Reporting AE/ARs that are related to the trial and unexpected, by email to the research ethics committee.
4. Reporting safety information to the independent oversight committees identified for the trial (Data Monitoring and Ethics Committee (DMEC) and/or Trial Steering Committee (TSC)) according to the Trial Monitoring Plan.
5. Preparing standard tables and other relevant information in collaboration with the CI and ensuring timely submission to the MHRA and REC.

### 12.6 Reporting urgent safety measures

If any urgent safety measures are taken, the CI shall immediately, and in any event no later than 3 days from the date the measures are taken, give written notice to the REC, Sponsor and other appropriate bodies where relevant (e.g. MHRA) of the measures taken and the circumstances giving rise to those measures.

### 13. RISK MANAGEMENT

### 13.1 Risk assessment and reporting

Prior to study inclusion we explicitly ask and screen for symptoms of distress, wellbeing and poor mental health (including symptoms of depression, suicidal risk). Whether meeting exclusion criteria at screening or indicating risk at follow up, participants will be provided with automatic feedback with suggested sources of help such as the recommendation to consult their GP or weblinks or phone numbers for national NHS services or those relevant to the Armed Forces Veterans Community.

### 13.1.1 Risk management during baseline assessment

The second screening (i.e., baseline assessment) will allow those with elevated risk to access help pages linking to sources of support as soon as possible. Participants are given the following automated paragraph and options:

**University of Exeter Qualtrics page automated message:**

This study aims to examine the potential for effectiveness of a mobile phone application adapted for female Armed Force Veterans for the management of depression or generalised anxiety. If you are currently struggling with suicidal thoughts or traumatic experiences the trial would not be right for you and specialist help would be the best option. If these issues are affecting you now then we would urge you to reach out to family, friends, or your family doctor/general practitioner. Click the relevant button below for additional links to relevant helpful information and support services available to you. Signposting information detailed earlier will be provided with contact information.

### 13.1.2 Risk management in trial

Once the participant joins the study and starts to use either of the apps, risk is managed by the participant selecting the SOS button or being directed to the SOS button in the event that either PHQ-9 has increased >1 or score has increased >20. Each occurrence of elevated symptomatology (PHQ-9>20) or risk (PHQ-9-Q9>1) when using either app will be logged by the electronic system, the Lead Researcher notified and recorded as an AE.

We note that the nature of the high level of confidentiality means that we do not have relevant GP or family doctor details for participants. The default response is direct information disclosure to the participant of a potential clinical issue with signposting information provided. Transmission of the collected information to the GP will not be possible and requesting this information a priori would negate the ethical and recruitment benefits of pseudo-anonymity and confidentiality for participants. Based on recent recommendations, our default policy is to inform participants of the possibility of them being at risk and to recommend they seek help. This is to prioritise their welfare.

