### 10.2 Outcome measures

**Table 11 Outcome measures**

| **Measure** | **Description** | **Reliability and Validity** |
| --- | --- | --- |
| **Primary/Feasibility/Methodological Outcomes** | | |
| **Feasibility** | To collect data on number of participants consented, recruited, completed screening, and to assess recruitment method, measure completion (baseline, 6 weeks, 10 weeks), drop out, drop out reason | NA |
| **Secondary Outcomes** | | |
| **Patient Health Questionnaire-9** (**PHQ-9**; Kroenke et al., 2001) | 9-item participant rated questionnaire assessing frequency of symptoms of depression over the last 2 weeks. 4-point scale for each item, with anchors at 0=not at all, 1 = several days, 2= more than half the days, 3 = nearly every day. Unidimensional scale. Available in English, Spanish, German, and Dutch versions. | Leading measure of depression widely used in clinical trials, clinical practice, and as part of the NHS Quality and Outcomes Framework (QOF) for UK primary care and Improving Access to Psychological Treatments (IAPT) Minimum Data Set (MDS). Cronbach’s α =0.89 in primary care, test-retest reliability (ICC) 0.84 after 48 hours. Validation studies indicate positive correlations with measures of functional status (r=0.73), disability days (r=0.39), and symptom-related difficulty (r=0.55) At cut-off of ≥ 10, excellent specificity (0.88) and sensitivity (0.88) with diagnoses of major depression by structured interview, replicated in a UK population (sensitivity 0.80; specificity 0.92). |
| **Generalised Anxiety Disorder-7 (GAD-7**; Spitzer et al., 2006) | 7-item participant rated questionnaire assesses frequency of symptoms of anxiety over the last 2 weeks. 4-point scale for each item, with anchors at 0=not at all, 1 = several days, 2= more than half the days, 3 =nearly every day. Unidimensional scale. Available in English, Spanish, German, and Dutch versions. | Leading measure of anxiety widely used in clinical trials, clinical practice, and as part of the UK NHS IAPT MDS. Cronbach’s α =0.92, test-retest reliability ICC = 0.83. Convergent validity good, r =.72 with Beck Anxiety Inventory, r = 0.74 with Symptom Checklist-90 anxiety scale. |

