### 12. ADVERSE EVENTS

### 12.1 Participant welfare and safety

There is no known health risk associated with any of the assessments or either IonaFFV or Iona SHAM CONTROL. The risk concerning participation in this study is believed to be low. Further, we anticipate that IonaFFV will reduce low mood or worry. In our experience from previous projects, participants are happy to participate and enjoy the assessment tasks. We will strive to use tasks that the participants experience as motivational and reinforcing whenever possible. This will also ensure a low attrition rate.

Because the trial is only focussed on people with mild to moderate depression or anxiety, the initial screening process will exclude anyone with a history of severe psychiatric disorder and those reporting elevated suicidality (PHQ-9>1). These individuals will be automatically guided towards appropriate information and sources of help. This process means that individuals likely to have significantly increased risk (e.g., for self-harm and suicidality), and/or for whom more intensive psychological and psychiatric treatment is appropriate, will not be included in the study.

Other than the intervention failing to produce an effect, there is nothing in the literature to suggest possible adverse effects of the assessments and interventions. As with all psychological interventions, individuals reflect on their difficulties, which can produce temporary increases in distress, but no more than would commonly occur in daily life. Versions of techniques within the intervention are commonly adopted within a general adult version of the Iona app previously employed as in an NHS Talking Therapies for anxiety and depression service and with no detected harmful effect. As such, the intervention within the trial may benefit individual participants. The likeliest outcome for users who do not find the intervention of benefit is their disengagement from it. In addition, all participants receive more intensive monitoring, with processes within IonaFFV and Iona SHAM CONTROL to identify and direct all relevant participants to potential sources of help.

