### 12.2 Risk management processes

As part of our policy for addressing risk and prioritising the welfare of participants there are 2 main processes in place.

The main indicators of harm will be completion of the PHQ-9 questionnaire by the participants in both study arms at all assessments (baseline, 6 weeks, 10 weeks). The PHQ-9 study questionnaire will be automatically screened by the AI function of the apps for signs of distress (defined as scores above 20 on PHQ-9 for depression or reports >1 on Question 9 of the PHQ-9). Outside of the research there is also a function within the apps to identify aspects of risk and through the SOS button, which if selected will automatically provide participants with recommended advice and signpost towards help (e.g. NHS and Armed Forces specific support services).

We will record all occasions where risk within IonaFFV or Iona SHAM CONTROL app has been highlighted and recorded and reported to the Trial Management Group and Sponsor to determine whether events are related to the treatments and to take appropriate action.

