### 13.3 Identifying suicide risk

These are 4 ways within the study that a participant could indicate risk; (1) prior to consent; (2) prior to using the app; (3) end of treatment; (4) follow-up assessment. However, as part of the routine functioning of the Iona EXSW or Iona SHAM CONTROL during use where PHQ-9 increases above 1.

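### Section 13.1.2 words the in-app SOS trigger as an increase and names no item for suicide risk, in conflict with the level rules in its next sentence and in 12.2

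*Protocol*

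**What the plan says.** Section 13.1.2 of the protocol covers risk once a woman is using either app. Risk is handled by her choosing the SOS button herself, or by her "being directed to the SOS button in the event that either PHQ-9 has increased >1 or score has increased >20". The first limb names no item of the questionnaire, and both limbs speak of an increase.

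The sentence that follows sets the recording rule: "Each occurrence of elevated symptomatology (PHQ-9>20) or risk (PHQ-9-Q9>1) when using either app will be logged". The Lead Researcher is then notified and an adverse event is recorded. That rule is a pair of levels, with Question 9 named. Section 12.2 gives the distress signals for which the apps screen in the same form: "defined as scores above 20 on PHQ-9 for depression or reports >1 on Question 9 of the PHQ-9".

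Other sections also use the level of Question 9. Sections 11.8 and 13.4 tie leaving the trial to a score of 2 or 3. Section 12.4 separately records moves from 0 or 1 to 2 or 3. Table 8 (Section 7) admits women with a PHQ-9 total of 5 to 19 and a Question 9 score of 0 or 1.

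Two further sections leave Question 9 out. Section 13.3 refers to risk arising "during use where PHQ-9 increases above 1", and Section 12.1 describes the women to be screened out as "those reporting elevated suicidality (PHQ-9>1". Both are thresholds rather than changes, but as written they apply to the whole questionnaire.

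**The concern.** The apps have no human support (the TIDieR table in Section 9.1). Section 13.1.2 adds that no GP details are held and that the default response is automated signposting. The SOS trigger is therefore the step that reaches the woman, and its wording matters more than it would where a clinician reads the scores.

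As written, the rule that directs a woman to SOS and the rule that logs her as an adverse event, in consecutive sentences, can give opposite answers for the same record. Anyone programming or checking the apps has several versions to choose from. Section 12.2 has all in-app risk occasions recorded and reported to the Trial Management Group and Sponsor. If direction to SOS and logging follow different rules, those reports become hard to interpret.

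**Working it through.** The protocol states no firing rate for this trigger, so there is no figure to reproduce. The check compares the possible readings and then sizes one of them.

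**Inputs.** The PHQ-9 is a "9-item participant rated questionnaire assessing frequency of symptoms of depression over the last 2 weeks", with a "4-point scale for each item, with anchors at 0=not at all, 1 = several days, 2= more than half the days, 3 = nearly every day" (Table 11), so the total runs from 0 to 9 × 3 = 27. Entry totals are 5 to 19, which is 15 possible scores, with Question 9 at 0 or 1 (Table 8). Test-retest ICC is 0.84 over 48 hours (Table 11). Scheduled follow-ups are at weeks 6 and 10. The PHQ-9 SD is not given; 3 to 6 is **assumed**. A uniform spread over 5–19 would give 4.3.

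**1. Readings of the first limb.** Two things are open: the quantity (total or Question 9) and the type of rule (rise or level). The last column is the level rule in the next sentence of 13.1.2 and in 12.2.

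| Record | Rise in total >1 | Total above 1 | Rise in Q9 >1 | Q9 above 1 | Level rule (total >20 or Q9 >1) |
|---|---|---|---|---|---|
| Total 12→14, Q9 0→0 | directed | directed | no | no | not met |
| Total 12→12, Q9 0→2 | no | directed | directed | directed | met |
| Total 12→12, Q9 1→2 | no | directed | no | directed | met |

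Only the fourth reading agrees with the level rule throughout, and it requires the reader to supply both the item and the level. The second is met by every entrant at baseline, since the lowest eligible total is 5. The same holds for the wording in 12.1 and 13.3.

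**2. The second limb read as a rise.** A rise above 20 from entry score b needs 27 − b > 20, so b < 7. It is possible from 5 (27 − 5 = 22) and 6 (27 − 6 = 21), and impossible from the other 13 of 15 entry scores. However, the limbs are joined by *or*. A total above 20 is at least 21, and 21 − 19 = 2, so any such woman has risen by at least 2 and meets the first limb read as a rise in the total. A woman going from 15 to 24 is directed by that limb.

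**3. Rise in the total with no true change (illustrative).** SD of the difference = SD × √(2 × (1 − 0.84)) = 0.566 × SD. P(rise ≥ 2) = 1 − Φ(1.5 / SD of difference), with continuity correction. For SD 4: 0.566 × 4 = 2.26; 1.5 / 2.26 = 0.66; probability 25.4%. The two-visit figures are simulated with a shared baseline error.

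| Assumed SD | One follow-up | Either of two |
|---|---|---|
| 3 | 18.8% | 29.7% |
| 4 | 25.4% | 38.4% |
| 4.3 | 26.9% | 40.3% |
| 5 | 29.8% | 44.1% |
| 6 | 32.9% | 47.8% |

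A second simulation used whole-number scores, population means of 8 to 12 and selection on a baseline of 5–19. It gave 17–33% at one follow-up and 27–48% at either. With an assumed ICC of 0.70, for an interval longer than 48 hours, it gave 23–37% and 35–53%.

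**The case against.** The strongest reply is that this is a drafting slip beside its own correction. The next sentence of 13.1.2 gives levels and names Question 9. Section 12.2 says the same, and 11.8, 12.4 and 13.4 all use Question 9. An increase of >20 can naturally be read as having risen above 20, which makes that limb sound. This stands as evidence of the probable intent. It does not make the sentence usable as a specification, because the suicide limb needs both the item and the type of rule supplied.

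A reader might infer four stronger things, none of which the documents support.

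- *Severe totals go undirected because the >20 limb cannot fire for most entry scores.* On the literal reading the >1 limb catches every total above 20. Missing one needs a mixed reading, with Question 9 supplied in the first limb and a literal rise kept in the second. The protocol gives no ground for choosing that.
- *The adverse-event record is corrupted.* Logging in 13.1.2 and discontinuation in 11.8 and 13.4 are defined by level. Section 13.4 also logs suicide risk shown at follow-up.
- *Section 12.1 excludes every woman.* Eligibility is set by Table 8, which names Question 9.
- *A quarter or more of women would be flagged by noise.* That rests on an SD the protocol does not give. At one follow-up with ICC 0.84, the analytic calculation needs an SD of about 3.9 or more.

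The rates also apply to weeks 6 and 10, where 13.4 and 13.5 give their own level rules for the Qualtrics page. The frequency of PHQ-9 completion during app use is not stated, and nothing says which section the apps are coded from.

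**Conclusion.** The point holds as a contradiction about who is directed to SOS. The trigger sentence in 13.1.2 disagrees with its next sentence and with 12.2. Sections 12.1 and 13.3 compound this by leaving out Question 9, though they do not state a change rule. The table of readings and the arithmetic on the second limb need only the scoring range and entry window in the protocol.

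The rates of 17–33% at one follow-up and 27–48% at either of two are an illustration of the reading as a rise in the total. They assume no true change, the 48-hour ICC of 0.84 and an SD of 3 to 6. The 48-hour ICC is probably generous for 6 to 10 weeks, which would make the rates too low. The correction is worth making because the trigger is automated and no person stands behind it.

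**What to change.** Reconcile Sections 12.1, 13.1.2 and 13.3 with 12.2 so that a single statement of the trigger is used throughout. It should name the quantity for each limb (Question 9 or total score) and say whether the rule is a level or a change from baseline. Use that statement for both SOS direction and adverse-event logging, and check the code of both apps against it before recruitment. Which clinical rule applies is for the investigators to settle.

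The cost is a wording correction in three sections and a check of the trigger code in two apps. No change to sample size, visits or analysis is needed.

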### 13.2 Preventing abuse of participants and risk analysis

Our risk analysis indicates potential theoretical risks and opportunities for abuse of the research findings and of participants within the study including psychological harms (e.g., distress), invasion of privacy (e.g., intrusion into private affairs, public disclosure of embarrassing private information, publicity that puts the individual in a false light to the public, or appropriation of an individual’s name or picture for personal/commercial advantage), loss of confidentiality (personal data becoming public through error or thorough deliberate hacking), and social harms (e.g., embarrassment, stigmatisation). The risk analysis indicates that the likelihood of these risks occurring is relatively low although any potential impact for participants would be high, and, as such, we will enact a detailed participant risk register and update it regularly through the project. Multiple steps and processes will be put into place to mitigate and minimise these risks including (a) explaining potential risks in the information sheet; (b) the welfare procedures described above to minimise participant distress; (c) high levels of security and the use of privacy by design protocols for the app and database; (d) a privacy impact assessment; (e) the emphasis on confidentiality in the project and the separation of collected data from personal identifiers; (f) the use of a code of conduct for all researchers.

In this trial no medical care is provided regardless of the level of risk presented. This is because this trial is for people seeking to manage low mood or excessive worry in a self-help intervention for people with no current risk or have experienced a traumatic episode in the last month. Participants are advised of this at the beginning of the respective app, on the information sheets and sign the section on the Consent Form to confirm that they understand this.

### 13.3 Identifying suicide risk

These are 4 ways within the study that a participant could indicate risk; (1) prior to consent; (2) prior to using the app; (3) end of treatment; (4) follow-up assessment. However, as part of the routine functioning of the Iona EXSW or Iona SHAM CONTROL during use where PHQ-9 increases above 1.

### 13.4 University of Exeter Qualtrics page at second screening (as baseline), 6 and 10 week follow up

A recruit may indicate risk on the website during the baseline assessment or 6 weeks treatment end or 10 weeks follow up in response to questions about suicidality. If the participant scores 2 or 3 on the PHQ-9 Q9, the participant will be encouraged to seek support from family or friends, GP or signposting information to NHS or female Armed Forces signposting information will be provided.

PHQ-9-Q9

Over the last two weeks, how often have you been bothered by any of the following problems? Thoughts that you would be better off dead, or of hurting yourself in some way?

Those scores would represent the answers several days (1), more than half the days (2) and nearly every day (3)

If the potential participant answers yes to either more than half the days (2) or nearly every day (3) to either question, then they would be removed from the trial and automatically presented with the following risk screen:

